### 2.3. Participants

The study aims to recruit ESKD patients undergoing peritoneal or hemodialysis treatment.

Inclusion criteria: males and females patients aged ≥18 years; able to walk for at least 6 m; performing dialysis for at least 3 months in stable conditions; Mini Mental Status Examination score ≥18/30 sufficient to enable patients to give informed consent.

Exclusion criteria: uncorrected anemia (hemoglobin concentration <9 g/dL); acute infectious disease (C-reactive protein > 10 mg/L), severe cardio-respiratory (e.g., unstable angina; severe heart failure identified by New York Heart Association class III-IV), musculoskeletal or neurological conditions (e.g., lower limbs major amputation) inhibiting exercise training.

As this is an implementation feasibility trial, the exclusion criteria are kept at a minimum.

During the first meeting with potential participants, the study personnel will check patients’ interest in taking part in the study; if a positive response is provided, a screening visit to verify compliance with the inclusion criteria will be executed. Patients meeting the eligibility criteria will be given a letter explaining the study, as well as the consent form, and they will be encouraged to ask any questions. Within seven days, patients will be asked to return a signed copy of the consent form; if the patients have not yet decided, they will be given adequate time to consider their participation. According to the guidelines [26], the total number of screened subjects who are ineligible (and the reasons for their ineligibility) or not willing to participate in the study (along with the reasons and the main clinical characteristics, if provided) will be tracked.

Preparticipation screening with exercise testing will not be regularly scheduled due to the low intensity of the exercise program proposed, as it was designed for special populations [27].

For those who volunteer to participate, baseline outcome measurement sessions will be scheduled within two weeks. In this timespan, patients will be provided with a wrist fitness tracker to be worn continuously for 6 days, including at night and during resting periods. The number of daily steps, number of hours of sleep or rest and heart rate will be recorded.

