According to each patient’s baseline physical activity level, a semipersonalized walking program will be provided. This program, derived from previous experience with ESKD patients [13,29] was also successfully tested in other fragile populations such as stroke survivors or multiple sclerosis patients [30,31,32]. The training program will be performed at home at a prescribed speed and it includes a 10-min session/day of intermittent walking (1- or 2-min work and 1-min seated rest). The speed which is converted into a walking cadence is increased weekly and it is controlled at home with the aid of a metronome (Table 2). Patients will be provided with a daily log containing the detailed exercise prescription and free lines to provide feedback on training execution and any possible related symptoms.

Structured supervised low-intensity exercise (S-SU-LI)

Patients will meet at a specified location (room or corridor) into the dialysis unit for the exercise program in groups of a maximum of four subjects. The thirty-minute training session will be scheduled on a 2- or 3-time/week pattern, and they will be performed immediately before or after the dialysis treatment or according to patients’ preferences and considering the postdialysis fatigue that affects this population [33].

Each session will include low-intensity walking exercises (similar to those for the structured home-based training) and resistance and power exercises with elastic bands and ankle/wrist weights. Each session will begin and end with a warm-up and cool-down period of stretching, respectively. The total duration of the session will be approximately 30 min. The training intensity will be set according to the patient’s baseline capacity and it will be weekly increase. The rate of perceived exertion will be always collected (Table 2).

Physical performance assessment only (PPA)

Patients choosing this option will not begin any exercise program, but they will perform the outcome measures session only. A switch to another treatment, periodically proposed by the EF, will be always possible.

Study design is presented in Figure 1.

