### 3.6. Phase 2 Outcomes

First, the feasibility and safety of the exercise programs will be assessed in terms of adverse events, falls and intercurrent problems. In addition, the adherence of each patient to the selected training option will be determined by analyzing the number of sessions completed, the total minutes of training and the percentage of patients that reached the amount of physical activity indicated by the guidelines.

Quantitative outcomes will be collected before the beginning of the training program, at the end of the training program (three months) and at the six-month follow-up.

The primary outcome will be exercise capacity, assessed through the 6-min walking test. Subjects will be instructed to walk with their habitual walking device as far as possible in 6 min. The test will be performed on a 22-m walkway. The patients will have the possibility of slow down and rest if necessary. The total distance walked, the pain-free walking distance and the perceived exertion at the end of the test (Borg Scale 1–10) will be recorded [34] (Table 1).

Secondary outcomes will include the following:Gait speed, assessed through the 10-m walking test.Lower limb strength, evaluated with the 5-time sit-to-stand test.Health-related QoL, measured by the Italian version of the Short Form Health Survey (SF-36).Fear of falling, assessed through the Short Falls Efficacy Scale.Estimated functional capacity, measured by the Duke Activity Status Index.Depression, evaluated by the Beck Depression Inventory—II and the demoralization scale.Heart rate, oxygen saturation and blood pressureLaboratory outcomes: Serum creatinine levels, estimated glomerular filtration rate, Kt/v, glycaemia, total cholesterol and a full blood count will also be determined.Long-term outcomes: Other clinical outcomes, such as mortality and all-cause hospitalization, will be recorded at 3, 6, 12 and 24 months from the end of the exercise program.

A detailed description of secondary outcomes is available in the Supplementary Material 1.

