### 3.10. Statistical Analysis

In the first qualitative phase, descriptive statistics, chi-squared tests and mixed models of analysis will be employed. Regression analyses will be conducted to determine if different variables (e.g., distance from dialysis center and presence of a caregiver) might interfere with patients’ decisions. Furthermore, the physical activity level and physiological and psychological variables assessed at baseline will be considered independent variables in the regression models.

In the second phase, standard methods of analysis for clinical trials will be used. First, baseline comparisons of patient characteristics for each group will be compared for demographics and primary and secondary outcome measures. The data distribution will also be verified through a Shapiro–Wilk test. A two-way repeated measure analysis of variance will be used to compare differences in the primary and secondary outcomes. Within-group comparisons will be performed via paired Student’s t-tests or Wilcoxon tests, as appropriate. If a significantly different distribution between the baseline characteristics of the group is identified, a secondary analysis that employs multivariate modeling to adjust for these factors will be performed (e.g., linear mixed models for repeated-measures analyses with unbalanced design). Moreover, Kaplan–Meier analysis and Cox regression will be used to model incidence rates for long-term clinical outcomes (hospitalization rate and death). Finally, a post hoc power analysis will also be carried out to determine the clinical impact of the findings.

All analyses will be conducted using intention-to-treat. Missing values, though we will make any effort possible to reduce their incidence, will be treated using the multiple imputation procedure. Moreover, a per-protocol analysis to assess the stability of the study’s conclusions will also be performed. Properly gender-oriented analyses will be carried out for most of the outcomes. A *p* value of 0.05 will be considered statistically significant.

Statistical analysis will be performed with SPSS 21.0 (IBM, Armonk, NY, USA) and MedCalc statistical software (version 19.4.0 and following, MedCalc Software bvba, Ostend, Belgium).

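### Estimated GFR is listed as an outcome although every participant is on dialysis, and Kt/V is listed as one outcome across hemodialysis and peritoneal dialysis; eGFR should be dropped or replaced, and Kt/V analysed by modality (minor)

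*Protocol article*

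**What the plan says.** On the population, section 2.3 states: "The study aims to recruit ESKD patients undergoing peritoneal or hemodialysis treatment". The inclusion criteria add "performing dialysis for at least 3 months in stable conditions", so nobody enters before dialysis has started.

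On the outcomes, the laboratory items in section 3.6 are part of the secondary outcomes: "Serum creatinine levels, estimated glomerular filtration rate, Kt/v, glycaemia, total cholesterol and a full blood count will also be determined". Kt/V carries no modality or time base, and no method is named for the estimated GFR. Timing is given as "Quantitative outcomes will be collected before the beginning of the training program, at the end of the training program (three months) and at the six-month" time point, and Table 1 schedules the biochemical markers at those three visits. Section 3.6 refers to Supplementary Material 1, which is not among the documents at hand, for details of the secondary outcomes.

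On the analysis, section 3.10 says: "A two-way repeated measure analysis of variance will be used to compare differences in the primary and secondary outcomes", and "Within-group comparisons will be performed via paired Student’s t-tests or Wilcoxon tests, as appropriate". It also compares the groups at baseline on the outcome measures. Adjustment is conditional: "If a significantly different distribution between the baseline characteristics of the group is identified, a secondary analysis that employs multivariate modeling" is then added. Dialysis modality is not named as a factor anywhere in that section. The Introduction calls the comparisons of functional and clinical parameters exploratory and secondary to the feasibility aims.

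**The concern.** Two listed outcomes do not fit the population as the analysis would use them.

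**Estimated GFR.** Estimating equations take serum creatinine to be in steady state and cleared by the kidney. In a dialysis patient it is cleared largely by the dialyzer or the peritoneum. In hemodialysis it also falls and rises around each session, and it depends on muscle mass. This is general method knowledge, not a statement in the documents. A number called estimated GFR, computed from such a value and compared between exercise arms, invites a reading about kidney function that it cannot bear.

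**Kt/V.** By convention it is a per-session quantity in hemodialysis and a weekly quantity in peritoneal dialysis. One outcome across both modalities mixes two scales. Patients choose their own arm, and the supervised program takes place in the dialysis unit around sessions, so the modality mix may well differ between arms.

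At stake is the reading of two exploratory laboratory results. An arm difference could be reported as an effect of a program when it arises from sampling time, muscle mass or modality mix.

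**Working it through.** The plan gives no figure for either parameter, so there is nothing to reproduce. The check sets the sections side by side and adds illustrations with assumed inputs.

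**1. Premises.** Sections 2.3, 3.6 and 3.10 together give an all-dialysis cohort with two modalities, one eGFR and one Kt/V at three visits, and an ANOVA with no stated separation by modality.

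**2. Is the eGFR creatinine-based?** The article does not say. The item is labelled as estimated, directly follows serum creatinine, and sits among blood tests with no urine collection listed. A creatinine-based value is the natural reading but remains an inference.

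**3. How eGFR would move (illustration).** Assume that eGFR varies as creatinine to the power −1.2.
- Creatinine 5% higher: 1.05^−1.2 = 0.943, a fall of about 6%.
- Creatinine 10% higher: 1.10^−1.2 = 0.892, a fall of about 11%.
- Post-dialysis instead of pre-dialysis draw, creatinine assumed 50% or 70% lower: 0.50^−1.2 = 2.30 and 0.30^−1.2 = 4.24, so the computed eGFR is multiplied by 2.3 to 4.2 in the same patient.

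These show sensitivity; they are not forecasts. The documents give no expected creatinine change and do not suggest that draws will alternate between pre- and post-dialysis. Analysing within-patient change does not remove these artefacts, because they are themselves changes over time.

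**4. Where the Kt/V scale gap matters.** Let g be the gap between the modalities' scales and p the share of peritoneal patients in an arm, with a constant g and no change of modality.
- Arm mean at any visit = common level + g × p, so the spurious difference between arms A and B is g × (pA − pB).
- Change within a patient: g is subtracted from itself, so the contribution is 0. Paired tests and the group-by-time term are not biased.
- Between-patient variance gains g² × p(1 − p), which enters the error term for the group main effect.

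With assumed values of g:

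| Assumed g | 10-point difference in p | 30-point difference in p |
|---|---|---|
| 0.2 | 0.02 | 0.06 |
| 0.4 | 0.04 | 0.12 |
| 0.6 | 0.06 | 0.18 |

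The documents give neither g nor the peritoneal share. Section 3.8 gives only a total of approximately 140 dialysis patients.

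**5. Planned uses affected.** These are the baseline comparison of arms, the ANOVA group main effect and the between-patient variance. Separately, one unit of change in Kt/V does not mean the same in the two modalities, so even an unbiased average change is hard to read.

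**The case against.** The strongest objection is that the article leaves the detail of the secondary outcomes to Supplementary Material 1. A condensed article may properly omit the eGFR method, the Kt/V definition by modality and the draw time, so their absence is not an error. This stands for Kt/V and for draw timing: the supplement may already settle both. It does not rescue a creatinine-based eGFR, since no further detail would make it a measure of kidney function in a cohort wholly on dialysis. If residual clearance was meant, the label is what needs changing.

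A second objection is that section 3.10 provides for adjusted models. Those could include modality, but they are secondary, depend on a significant baseline difference, and do not name it.

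Three stronger readings are tempting and are not supported:
- A reader might infer that neither parameter can be validly derived. Kt/V is valid within each modality, and no eGFR equation is named.
- A reader might infer that modality mix biases every planned test. A constant offset cancels in the paired tests and in the group-by-time term.
- A reader might infer that the eGFR artefact will count against the supervised arm. That arm does include "resistance and power exercises with elastic bands and ankle/wrist weights", but the article sets no aim for muscle mass, lists strength rather than muscle mass as an outcome, and Table 2 shows loads of 0.5 to 3 kg over 12 weeks. The direction is possible but not established. Nor does the plan say that eGFR will be read as renal harm or benefit; section 3.6 defines safety by adverse events, falls and intercurrent problems.

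**Conclusion.** The point holds in limited form and is minor. As listed, a creatinine-based eGFR cannot be read as kidney function in these patients, so its planned comparison over time and between arms is uninterpretable. Kt/V is sound within modality but should not be pooled as one outcome on mixed scales. The damage lies in baseline arm comparisons, the group main effect, the pooled between-patient variance and the meaning of a unit change.

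The conclusion rests on three assumptions: that eGFR is computed from creatinine, that Kt/V is recorded on each modality's conventional scale, and that Supplementary Material 1 does not already separate the modalities. The sizes shown are illustrations from assumed inputs. The primary outcome and the feasibility, adherence and safety aims are untouched.

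**What to change.** First check Supplementary Material 1. Unless it already does so:

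- Remove eGFR from the outcomes compared, or replace it with a named measure of residual kidney function if one is already collected.
- Keep serum creatinine, state that it is not interpreted as kidney function, and use the same draw time relative to dialysis at every visit.
- Analyse creatinine and Kt/V by dialysis modality. For Kt/V, the alternative is to convert it to one weekly standardized scale before comparing arms.

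The cost is a change of wording, with no extra samples. One uninformative outcome is lost, and the modality strata are smaller and so less precise. If one stratum is very small, it can only be described.

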### 3.7. Blinding

Outcome assessors will be blinded to group allocation, and unblinding will not be permissible for these researchers. If a participant interrupts the chosen program before the 3-month scheduled limit for any reason, he/she will be invited, if possible, to carry out the outcome measurement session.

### 3.8. Sample Size

To the best of our knowledge, this is the first trial of this type exploring patient preferences about programs and comparing the outcomes for these programs. Therefore, a power calculation hypothesizing a better effect of one program compared to another could not be performed; in addition, the investigators do not assign the interventions, and they do not know a priori how many patients will select each training option.

Otherwise, we aim to recruit a sufficient number of participants to address the study’s implementation objectives. The Nephrology Unit at the University Hospital of Ferrara manages approximately 140 patients on dialysis. The entrance of new patients into dialysis service will be checked every 3 months. We will try to propose the programs to all eligible patients and hypothesize a 50% rate of acceptance, which might be progressively increased by word of mouth among patients.

According to a power calculation based on a theoretical responder rate of 50% and considering a margin of error equal to 5% and a confidence level of 90%, a total of 88 patients will be required to make the first qualitative phase of the study representative of the population.

To optimize recruitment, all members of the Nephrology Unit of the hospital will be informed about the trial during team meetings. Information on the study procedures will also be given to the CKD and ESKD support groups, which will share the study information through their newsletters and website.

The EF will be available daily in the dialysis room to encourage patient participation. Informative material will also be available in the Nephrology Unit wards.

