### 2.2. Study Setting

The study will take place at the two dialysis venues of the Operative Unit of Nephrology and Dialysis located in two different locations: at the University Hospital of Cona, Ferrara and at Città della Salute, Ferrara. All the interventions scheduled, as well as the outcome measure assessment, will be performed in a purposely selected space inside each dialysis center. The study follows two different phases, as described below, to be completed within 3 years.

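### The only sample-size figure, 88 patients, does not follow from its stated inputs, and the protocol does not say which population it assumes or whether it counts patients approached or enrolled

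*Protocol article*

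**What the plan says.** Section 3.8 of the protocol article declines a comparative power calculation, because the investigators do not assign the programs and cannot know how many patients will choose each. It then gives one figure for Phase 1. For a 50% responder rate it states: "considering a margin of error equal to 5% and a confidence level of 90%, a total of 88 patients will be required". Phase 1, it says, will then be representative of the population.

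The same section supplies the other relevant facts:

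- **Pool:** the unit "manages approximately 140 patients on dialysis".
- **Inflow:** "The entrance of new patients into dialysis service will be checked every 3 months". No number is given. Section 2.2 sets the whole study "to be completed within 3 years".
- **Uptake:** all eligible patients are to be offered the programs, and the investigators "hypothesize a 50% rate of acceptance, which might be progressively increased by word of mouth among patients".

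Section 3.1 names two Phase 1 rates with different denominators: consent among eligible patients, and choice of each program.

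**The concern.** A reader who puts the three stated inputs into the usual formula for the precision of a proportion does not get 88, with or without a correction for the stated pool. The section mentions no correction and no population size for it.

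The unit of the 88 is also unclear. A precision formula for the consent rate returns the number of eligible patients approached. But the surrounding text speaks of recruiting participants, which points to patients enrolled. The two readings differ by a factor of two at 50% acceptance.

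This is the only quantitative support for the trial's size. Under section 3.11 the research coordinator reviews recruitment and decides whether to stop or conclude the trial, so it matters what the target counts and what precision it buys.

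**Working it through.** **Inputs.** From section 3.8: p = 0.50, margin e = 0.05, 90% confidence (two-sided z = 1.645), pool N of about 140, acceptance 50%. From section 2.2: 3 years. Assumed, because the documents give no figure: 80%, 90% or 100% of the 140 are eligible, that is 112, 126 or 140.

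**1. Attempt to reproduce 88**

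- No correction: n0 = z² p(1−p)/e² = 1.645² × 0.25 / 0.05² = 270.6, so 271.
- With correction: n = n0 / (1 + (n0 − 1)/N). At N = 140: 270.6 / (1 + 269.6/140) = 92.5, so 93.
- Other conventions at the same margin do not help. One-sided 90% gives 165, or 76 with N = 140. Two-sided 95% gives 385, or 103 with N = 140.
- Solving for the population instead: N = 130 gives 88.0. So 88 fits a corrected calculation with N of about 130.

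**2. Precision that 88 delivers (p = 0.5, 90% confidence)**

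Uncorrected: 1.645 × √(0.25/88) = 8.8 points. Corrected: multiply by √((N − 88)/(N − 1)).

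| Population N | n required for ±5 | Half-width at n = 88 |
|---|---|---|
| No correction | 271 | ±8.8 |
| 140 (stated pool) | 93 | ±5.4 |
| 130 (not stated) | about 88 | ±5.0 |
| 126 (90% eligible, assumed) | 86.2, so 87 | ±4.8 |
| 112 (80% eligible, assumed) | 79.4, so 80 | ±4.1 |

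**3. If 88 means patients enrolled**

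- Expected from the current pool at 50% acceptance: 0.5 × 140 = 70, 0.5 × 126 = 63, 0.5 × 112 = 56.
- Acceptance needed to reach 88: 88/140 = 62.9%, 88/126 = 69.8%, 88/112 = 78.6%.
- Eligible patients needed at 50%: 88/0.5 = 176. That is 176 − 140 = 36 new eligible patients (12 a year over 3 years) if all 140 are eligible, or 176 − 112 = 64 (about 21 a year) if 112 are.

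**4. If 88 means eligible patients approached**

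Acceptance places no limit on the number. It is reachable if at least 88/140 = 63% of the pool is eligible. About 0.5 × 88 = 44 would then enrol.

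**5. What approaching everyone delivers for a wider population (no correction)**

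- 140 approached: 1.645 × √(0.25/140) = ±7.0 points.
- 112 approached: 1.645 × √(0.25/112) = ±7.8 points.

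**The case against.** The strongest reply is that 140 is the number on dialysis, not the number eligible. Section 2.3 excludes several groups, so the relevant N is smaller. About 130 would be 93% of an approximate 140, and at 126 or 112 eligible patients 88 more than meets ±5. This stands as a plausible origin for the figure. It does not make the figure reproducible, because neither an eligible N nor a correction is stated. It does mean that a reader should not infer that ±5% is missed outright. Even at exactly 140 the corrected miss is small: ±5.4 against ±5, or five patients.

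A reader might also infer that 88 enrolled patients cannot be reached. The documents do not support that. The ceiling of 70 holds only for a closed pool at fixed acceptance, whereas section 3.8 checks for new entrants and expects uptake might rise, over a 3-year study. If 88 is the denominator of the consent rate, acceptance does not constrain it at all. What stands is that, on the enrolled reading, the target relies on an inflow or a rise in acceptance that is not quantified.

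Finally, ±8.8 might be read as showing that the claimed precision is wrong by nearly a factor of two. That applies only to inference beyond this unit. Section 3.8 does not clearly claim such inference, and section 4.2 acknowledges limited generalizability.

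**Conclusion.** The figure 88 is not reproducible from what section 3.8 states: the inputs give 271, or 93 with a correction at the stated pool. It fits a population of about 130 that the article does not give.

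The size of the error depends on the inference intended. For this unit's patients it is minor: ±5.4 at N = 140, and no shortfall if about 130 or fewer are eligible. For dialysis patients more widely it is substantial, ±8.8 against ±5. These results rest on p = 0.5, the normal approximation and, for the corrected figures, simple random sampling from a fixed pool. That last condition sits awkwardly with a plan to approach every eligible patient and add new entrants.

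The failure to say what 88 counts is a separate defect, and it holds whichever population was meant. No hypothesis test or comparison of programs depends on 88, so the consequence is confined to the stated justification of size and the recruitment target.

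**What to change.** Rewrite the sample-size paragraph of section 3.8 and call it a precision calculation rather than a power calculation. Say whether 88 counts eligible patients approached or patients enrolled. Then choose one inference target and keep to it:

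- **(a) This unit's patients.** State the eligible N and that a finite-population correction is used, and correct the number to match: 93 if N = 140, or 87 or 80 if N is 126 or 112. If every eligible patient is in fact approached, say so, since the correction then leaves no sampling error for that pool.
- **(b) A wider dialysis population.** Drop 88 and ±5%, and state the precision that approaching all eligible patients delivers: about ±7.0 points at 90% confidence with 140 approached, or ±7.8 with 112 (assuming 80% eligibility).

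The two should not be mixed: 93 is a finite-population figure and ±7.0 is not.

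In a separate sentence, give expected enrolment: about 56 to 70 from the current pool at 50% acceptance, assuming 80% to 100% eligibility, plus new entrants, with the inflow expected over the study period.

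The cost is one reworded paragraph and, under (b), a less favourable stated precision. No extra patients are needed.

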## 3. Procedures

### 3.1. Phase 1

In this phase, the exercise facilitator (EF) will be set up in the dialysis center. He/she will be an experienced physiotherapist and/or qualified exercise specialist who will be active in the dialysis centers for a specified number of hours per day to counsel patients concerning their worries and answer questions concerning physical activity. The EF will be properly trained by the members of the Rehabilitation Medicine Unit at the University Hospital of Ferrara on the management of frail patients by having experience with severely disabled patients with different conditions before the beginning of the study.

Stakeholder involvement: The EF, in collaboration with the team members, will prepare the informative material for the project. Team members will arrange meetings with unit personnel and coordinators of patient groups to introduce the EF figure, to explain the aims of the project and to address doubts and questions.

After the baseline outcome assessment, the EF will propose one of the four interventions to the patients by means of a specifically designed brochure, which is explained in the following section.

Qualitative outcomes will be employed in the first phase (Table 1). The rate of patients providing consent compared to the number of eligible patients, as well as the rate of patients choosing each of the training options proposed, will be calculated to determine patients’ willingness to exercise and their preferences about training. The impact of the patients’ characteristics and other variables on the choice of the program will also be investigated.

### 3.2. Phase 2

The EF will ask each enrolled patient to select an intervention and thus enter into one of the following arms.

Unstructured physical activity (U-PA)

According to each patient’s baseline physical activity level previously measured, the EF will advise patients to start or increase their spontaneous activity by counseling them on total exercise time, mode, intensity and frequency as suggested by the guidelines [27,28] (Table 2). A log-book and a wearable physical activity monitor will be provided to each patient. The instruments have to be returned in the subsequent controls, to encourage adherence and objectively measure the exercise activities.

Structured home-based low-intensity exercise (S-HB-LI)

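### Section 3.8 says 88 patients make Phase 1 representative, but the calculation covers only the precision of the consent rate, and program preferences are observed in consenters alone

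*Protocol article*

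**What the plan says.** Section 3.8 (Sample Size) states that the unit "manages approximately 140 patients on dialysis" and that the investigators "hypothesize a 50% rate of acceptance". It takes "a theoretical responder rate of 50% and considering a margin of error equal to 5% and a confidence level of 90" per cent, and concludes that 88 patients are needed "to make the first qualitative phase of the study representative of the population".

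Other sections show who supplies the Phase 1 data:

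- **Program choice.** Section 3.2: "The EF will ask each enrolled patient to select an intervention". Table 1 places choices, and the factors related to them, at baseline, after consent.
- **Baseline measurements.** Under section 2.3, the baseline sessions and the activity tracker are for patients who have volunteered.
- **Regressions.** Section 3.10 plans models of patients' decisions. It names distance from the center and caregiver presence as examples, and adds that activity level and "physiological and psychological variables assessed at baseline will be considered independent variables in the regression models".
- **Decliners.** Section 2.3 tracks the number of patients not willing to take part, "along with the reasons and the main clinical characteristics, if provided".
- **Consent rate.** Section 3.1 calculates it against the number of eligible patients.
- **Limitations.** Section 4.2 expects selection bias in those enrolled and says that generalizability may be limited.

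**The concern.** A margin of error and a confidence level describe how precisely a proportion is estimated by random sampling. They say nothing about whether the people who agree to take part resemble those who do not. Section 3.8 turns the first property into a claim about the second.

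The claim matters because Phase 1 is meant to show what patients are willing to do and which programs they prefer. The programs are offered to all eligible patients, but a preference is recorded only for those who consent. If the sentence stands, a reader may take the choice shares as the preferences of the unit's dialysis patients. A reader may also take the regressions on fitness, activity and mood as an account of who takes up an exercise offer. The design supports neither reading.

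**Working it through.** **Step 1. What does 88 measure?** The inputs from section 3.8 are p = 0.50, margin e = 0.05, 90% confidence (z = 1.645) and a unit of N = 140. For the precision of one proportion:

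- Without finite-population correction: n0 = z² p(1−p)/e² = 2.706 × 0.25/0.0025 = 270.6.
- With correction: n = n0/(1 + (n0−1)/N) = 270.6/(1 + 269.6/140) = 92.5, so 93.

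The stated 88 does not follow from N = 140. It appears at N = 130: 270.6/(1 + 269.6/130) = 88.03. The article does not state that size, though it could be a count of eligible patients. With 88 out of 140 the 90% margin is 1.645 × √(0.25/88) × √(52/139) = 0.054, or 5.4 points. The discrepancy is a separate and smaller matter. What counts here is that the only quantity in the formula is the responder rate. Nothing in it bears on program choice or on the likeness of consenters to decliners.

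**Step 2. How many patients will have a recorded choice?** At 50% acceptance, 140 × 0.50 = 70 consenters, before counting the new dialysis patients whom section 3.8 plans to check for every 3 months. The article does not say whether 88 means patients approached or patients enrolled. If approached, 88 × 0.50 = 44 would choose a program. If enrolled, 88/0.50 = 176 eligible patients would be needed. On either reading, half of the eligible patients have no recorded choice.

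**Step 3. Which Phase 1 quantities exist for whom?**

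| Quantity | Consenters | Decliners |
|---|---|---|
| Consent or refusal | yes | yes, as a count |
| Program choice | yes | no |
| Activity, physiological and psychological baseline variables | yes | no |
| Main clinical characteristics | yes | only if offered |
| Distance, caregiver | presumably yes | not stated |

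A model of consent versus refusal needs regressors observed in both groups. The variables in the third row are not, so they can serve only in models of which program a consenter picks.

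**Step 4. How far can choice shares be carried over?** Let a be acceptance and s the share of consenters choosing an option. With nothing known about what decliners would have chosen, the share among all eligible patients lies between a·s (no decliner would choose it) and a·s + (1−a) (every decliner would). Only a = 0.5 comes from the plan. The other inputs are assumptions.

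| a | s (assumed) | Lower | Upper | Width |
|---|---|---|---|---|
| 0.5 | 0.40 | 20% | 70% | 50 points |
| 0.5 | 0.25 | 12.5% | 62.5% | 50 points |
| 0.8 (assumed) | 0.40 | 32% | 52% | 20 points |

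The width is 1−a. At a given acceptance it does not shrink as more consenters are added, so a patient count cannot supply representativeness.

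**The case against.** The strongest reply is that the protocol discloses selection and never promises more than it can deliver. Section 4.2 says that selection bias is likely and that generalizability may suffer. The abstract speaks of the characteristics and preferences of responders, which consenters' data can answer. The assessment-only option lets patients who do not want to train enrol and be counted, which may narrow the gap between consenters and decliners. On this view, one sentence is loosely worded.

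Much of this stands, and it rules out some stronger readings:

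- **That nothing can be learned about taking part.** The documents do not support this. The consent rate among eligible patients can be estimated, decliners' reasons and main characteristics are to be tracked in part, and distance and caregiver status are not said to be confined to consenters.
- **That responders have no comparison group.** They have one, but it is incomplete and depends on what decliners choose to offer.
- **That the 20% to 70% range shows the 5% margin to be wrong.** The margin belongs to the responder rate, for which a refusal is an observation and not a missing value. The article attaches no such margin to program shares, so the two figures should not be compared.
- **That the bounds show expected bias.** They are logical extremes. The upper one needs every decliner to favor the same option.

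The reply does not rescue the sentence. The example in section 4.2 concerns which program fitter or less fit enrollees choose, and its remedy is aimed at the lack of randomization between arms. It offers nothing for non-participation. Its caution about generalizability contradicts the claim in section 3.8 and leaves that claim in the text.

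**Conclusion.** The point holds in a limited form. Section 3.8 credits Phase 1 with a property that its calculation cannot confer and that section 4.2 in effect denies. Choice shares, and regressions on the baseline-measured variables, apply to consenters only, and those variables cannot explain consent versus refusal. The consent rate itself is not affected, provided that eligibility is also established for those who decline.

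On size, the plan's own 50% acceptance leaves about half of eligible patients without a recorded choice. The 20% to 70% range illustrates what that permits under an assumed 40% share. It is neither a forecast nor an estimate of bias. The conclusion does not depend on that share, nor on whether 88 or 93 is the right count. It rests only on acceptance falling well short of complete and on choice being recorded after consent, as the article describes. The correction is inexpensive and changes what Phase 1 may conclude, so it should be made.

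**What to change.** 1. In section 3.8, restrict the sentence to the precision of the consent rate among eligible patients and delete the claim of representativeness.
2. In sections 3.1 and 3.10, state that program choice and its predictors are reported conditional on consent, and that the baseline-measured variables enter only models of choice among consenters.
3. Compare participants with non-participants by standardised differences on routine fields such as age, sex, modality, venue and time on dialysis. Add a simple participation model if numbers allow. Take the fields from de-identified unit records where ethics approval permits, and otherwise from the characteristics tracked under section 2.3, stating how many decliners supplied them.
4. If bounds on choice shares are shown, label them worst-case illustrations under stated assumptions and keep them apart from the 5% margin. Weighting for participation is optional. With about 70 consenters spread over four options it could be unstable, and it adjusts only for recorded fields.

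The cost is a small data extract, one table and possibly an ethics notification. The downside is a more modest claim for Phase 1.
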